## Abstract

**Background:**

Sexual dysfunction can have a negative impact on women’s quality of life and relationships. There is limited information about female sexual function and treatment, particularly during pregnancy and the postpartum period. The effect of pelvic floor muscle exercise (PFME) on sexual function (SF) has not been studied adequately. The purpose of this study is to investigate the effect of antenatal PFME on female SF during pregnancy and the first 3 months following birth.

**Methods/design:**

This is a pragmatic, randomised controlled trial which will compare a structured antenatal PFME programme combined with standard antenatal care to standard antenatal care alone. Eligible women who are less than 22 weeks’ gestation will be recruited from the antenatal clinics of one hospital located in Western Sydney, Australia. A sample of 200 primiparous pregnant women who meet the inclusion criteria will be randomised to either control or intervention groups. This sample size will allow for detecting a minimum difference of 9% in the female SF score between the two groups. The duration of the PFME programme is from approximately 20 weeks’ gestation until birth. Female SF will be measured via questionnaires at < 22 weeks’ gestation, at 36 weeks’ gestation and at 3 months following birth. Baseline characteristics, such as partner relationship and mental health, will be collected using surveys and questionnaires. Data collected for secondary outcomes include the effect of PFME on childbirth outcomes, urinary and faecal incontinence symptoms and quality of life.

**Discussion:**

The findings of this study will provide more information on whether a hospital-based antenatal PFME has any effect on female SF, urinary and faecal incontinence during pregnancy and the first 3 months following birth. The study will also provide information on the effectiveness of antenatal PFME on childbirth outcomes.

**Trial registration:**

Australian New Zealand Clinical Trials registry, ACTRN12617001030369. Registered on 17 July 2017.

**Electronic supplementary material:**

The online version of this article (10.1186/s13063-019-3226-6) contains supplementary material, which is available to authorized users.

## Background

Sexual dysfunction is considered a public health concern [1, 2] and is defined as the disturbance in sexual desire and psychophysiological changes that characterise the sexual response and cause interpersonal difficulty and marked distress [3] which can affect the quality of life adversely [4]. The incidence of sexual dysfunction is estimated to range from 19 to 50% of the population, with a higher incidence in women (43%) than in men (31%) [5, 6].

It is reported in some studies that the incidence of sexual dysfunction rises to approximately 63–93% of all pregnant women [7]. Pregnancy and birth can cause significant life changes that alter previous phases of physical and emotional adjustment of couples and many women experience sexuality differently during this period [8].

About 90% of women claim to resume sexual activity 6 weeks after childbirth [9], and around 83% are reported to experience sexual problems in the first 3 months and 64% in the first 6 months following birth [9]. Acele and Karaçam [10] found that 91.3% of women experience at least one sexual problem in the postpartum period. Khajehei et al. [11] conclude that 64.3% of Australian women reported sexual dysfunction in the first year after birth and 70.5% expressed sexual dissatisfaction.

Sexual activity involves a complicated interaction of physiological, psychosocial and behavioural components in and between individuals [12]. Among several factors associated with sexual dysfunction (such as sleep deprivation, breastfeeding, fatigue, etc.) [9], loss of pelvic muscle strength is one of the physical changes which occurs in the postpartum period and may be present even years afterwards. This can result in pelvic pain, urinary incontinence, cystocele, rectocele and lack of sexual satisfaction [13]. Having healthy pelvic floor muscle strength (PFMS) is important for satisfactory genital arousal and orgasm. Weak muscles may not provide adequate stimulation and arousal, thus hindering orgasmic potential [14].

Women seeking assistance with sexual dysfunction find few options of care available to them [15]. Treatment of female sexual dysfunction is still an unmet clinical need. There are no Food and Drug Administration-approved treatments available for women [16]. PFME has been proposed to be a potential factor impacting on female SF. There may be a psychosocial effect of PFME, such as improved self-acceptance, body awareness and satisfaction [17, 18]. PFME contributes to increased blood flow to the pelvis and enhanced vaginal and clitoral receptivity and responsiveness, providing pleasure during intercourse for both partners. Some studies have shown that strong pelvic floor muscles may be associated with better orgasmic and arousal potentials, desire, excitement and vaginal lubrication [3, 8]. Despite this theoretical background there are limited randomised controlled trials (RCTs) on the effect of PFME on female sexual dysfunction [3], particularly during pregnancy and the postpartum period. Pauls et al. [8] suggested that pelvic floor muscle (PFM) training should be the first-line treatment for stress urinary incontinence and pelvic organ prolapse. However, there is a need for RCTs to test whether PFME can reduce sexual dysfunction [8].

The pelvic floor is a rich and dynamic system of interconnected muscles, nerves and ligaments that play a major role in maintaining urinary continence in childbearing women. During birth, the baby’s head stretches the surrounding structures and this stretching may result in damage to the muscles, nerves and connective tissues of the pelvic floor. An association between childbirth and urinary incontinence (UI) may be exacerbated by the use of forceps and can lead to long-term pelvic floor muscle dysfunction and urinary or faecal incontinence [19–21]. PFME before the labour and birth could produce strong and well-controlled muscles, reducing incontinence and even potentially reducing fatal malposition and malpresentation [22, 23]. Studies that examined the effect of PFME on labour show mixed results. There are studies demonstrating that women randomised to antenatal PFME had a lower rate of prolonged second stage of labour, less breech presentations and a lower episiotomy rate. The authors concluded that PFME appeared to facilitate rather than obstruct labour [23]. However, another study found no effect of PFME on the duration of the second stage of labour or the rate of instrumental birth [24]. There is additional evidence that PFME may have an effect on reducing faecal incontinence particularly at 1 year postpartum [25].

Therefore, a pragmatic parallel, randomised controlled trial was designed to investigate the effect of antenatal PFME on SF during pregnancy and the first 3 months following birth. The secondary objectives of this study are to investigate the effect of PFME on childbirth outcomes, urinary and faecal incontinence symptoms and specific quality-of-life measures during pregnancy and the first 3 months following birth.

## Methods

### Study design

A pragmatic, parallel RCT will be conducted to compare the effect of a structured antenatal PFME programme combined with routine antenatal care to routine standard antenatal care alone. The trial design incorporates treatment flexibility with the framework of a self-designed (semi-standardised) structured protocol of PFME. Any changes that need to be made to the trial protocol will be communicated to all investigators, the ethics committees and the trial registry. The protocol (version 1) has been designed in accordance with Standard Protocol Items: Recommendations for Interventional Trials (SPIRIT) guidelines for interventional trials [26] (Additional file 1) and will be conducted in accordance with the Declaration of Helsinki (1964) and the International Conference on Harmonization Good Clinical Practice (1996).

### Eligibility criteria

Low-risk primiparous women who present to the antenatal clinic for antenatal care will be approached to participate in the study. Women will be eligible if they are primiparous, over 18 years old, ≤ 22 weeks’ gestation, have a singleton pregnancy, anticipating a vaginal birth and have no history of urinary incontinence, pelvic surgery or pelvic organ prolapse at baseline. They also should have no previous history of depression, mental illness, alcohol and drug use or domestic violence and they need to be able to read, understand and communicate in English. Participants in the treatment group must also agree not to perform a PFME programme other than that provided in this study. Women will be excluded if they are over 22 weeks’ gestation, planning to give birth via caesarean section at the time of booking, multiparous, have a multiple pregnancy, have complicated pregnancies (type 1 and type 2 diabetic, vaginal bleeding, baby with abnormalities, etc.) and have known pelvic floor muscle dysfunction. Women who are not able to read and understand English to answer the questionnaires will also be excluded from this study.

### Recruitment, setting and informed consent

The recruitment will be undertaken at the antenatal clinics of a tertiary, teaching public hospital located in Western Sydney, Australia. The region includes a diverse population from diverse ethnic, cultural and economic backgrounds. Women will be recruited at the time of booking into the hospital or at their second antenatal visits when they are less than 22 weeks’ gestation. Pregnant women will be introduced into the study via flyers available in the antenatal clinics. The researcher will attach flyers to the files of all primiparous women less than 22 weeks’ gestation who are attending their first or second antenatal appointment. Midwives booking the women into the antenatal clinics will refer the women to the researcher, who will then provide women with detailed information about the research and confirm they are interested in joining the study. All women will be screened again to see whether they are eligible, and they will be provided with a participant information sheet and asked to provide written consent.

### Randomisation and blinding

It is not possible for study participants, and the first researcher ([name]) delivering the intervention, to be blind to the group allocations in this study. The other care providers, including midwives and doctors, will be blind to the group allocations. The first researcher ([name]) will assign women to the intervention or control groups using a centralised, remote computer-generated randomiser called Sealed Envelope [27]. To minimise the risk of detection bias, every woman will be issued with a unique four-digit study code. Therefore, the researcher ([name]) will be blinded to the participants’ responses using the study code during data entry. Additionally, data will be collected electronically and submitted by the women directly into the Red Cap database, which will further decrease the risk of bias. The first researcher ([name]) will be kept blinded to the group allocations during data analysis and the statistician will conduct the analysis with the researcher. There will be a treatment and control ratio of 1:1. All data including electronic and hardcopies will be destroyed 5 years after completion of the study according to NSW health policy.

### Treatment and assessment schedule (participant’s timeline)

The study period will run from approximately 20 weeks’ gestation until 3 months following birth. The duration of the PFME programme is from approximately 20 weeks’ gestation until birth. to assess the comparibility of the study groups, baseline information about demegraphic data, medical, surgical, psychological and family histories will be obtained from the hospital databse. Figure 1 outlines the process of the study.

**Fig. 1 Fig1:**
[figure not shown]
Pragmatic randomised controlled trial flowchart

### Intervention

#### Background

Various PFME protocols in non-pregnant women have been used in the literature. However, the number of repetitions and the duration of contractions and rest between series vary. The recommended frequency of PFME ranges from two to three times a week for up to a 3-month period, an amount of time necessary to obtain minimum hypertrophy and consequently muscle strength. Although various studies have confirmed the efficacy of PFME in the treatment of urinary incontinence, reports regarding PFME during pregnancy and the postnatal period are scarce [28]. According to Bø [29], those women who performed PFME with supervised training gain the most beneficial effect compared with those who do not receive training or supervision. About 200 million women around the world are not familiar with PFME. Moreover, it is reported that approximately 50% of women do not perform this exercise correctly [30].

PFME has been recommended as a first-line treatment for pelvic floor dysfunction, including urinary incontinence [14]. However, to date, there is no consensus about the most effective PFME regime to recommend to women, even from the most rigorously designed studies on urinary incontinence [31]. There is also conflicting information about whether using biofeedback to teach PFME is more effective than PFME alone. The study by Finnbogadóttir et al. [32] showed that women with a poor ability to contract their PFM had better PFMS when they were trained using biofeedback methods compared with those who received PFME alone. In contrast, Harvey [33] reported that antenatal PFMEs with biofeedback taught by trained personnel do not significantly reduce the incidence of postpartum urinary incontinence or improve PFMS in the short term. Fitz et al. [34] found that PFME alone led to a superior but not significant difference in the function of PFM when compared to PFME with biofeedback. This suggests that PFME with biofeedback is no more effective than PFME alone [34]. Compliance rates with PFME continue to be an issue [35, 36]. To increase the effectiveness of PFME, the recommended strategies include; appropriate follow up, feasibility of the program, training program, and patient-related actors such as motivation and commitment [35, 36].

#### Intervention used in this study

In this study, all women will receive standard antenatal care. In addition to routine antenatal education and care, the women in the intervention group will receive an initial education session on the function of PFMs and the benefits of PFME as well as how to perform PFME. Women will be provided with an additional pamphlet to read (version 06; published by the Continence Foundation of Australia) [37]. The duration of treatment is approximately from 20 weeks’ gestation until birth. The first training session will be conducted by the researcher and is designed to take 20–30 min. To design the PFME programme in this study, the researchers used a combination of information obtained from the physiotherapy department in the intended hospital setting as well as the recent literature available on PFME programmes. The final PFME programme in this study was developed using six references: effective functional motor activation patterns (the Knack method) [38, 39] and the studies carried out by Elbegway et al. [13], Mørkved et al. [22], Mørkved and Bø [40] and Alves et al. [41] (Fig. 2).

**Fig. 2 Fig2:**
[figure not shown]
Instructions for women. PFM pelvic floor muscle, PFME pelvic floor muscle exercise

The women will be instructed how to lift their PFM up and inwards around the urethra, vagina and rectum, squeeze as hard as they can and hold it for 8–10 s before relaxing the muscles gently. Women will be asked to keep breathing in and out during the contractions [40]. Women will be instructed to perform PFME in different positions so they can choose the most comfortable position to practise PFME at home (Table 1). Performing the proposed PFME at home is estimated to take 15 min.Sit with your legs apart and your back straight. Lift upwards and inwards around the openings in the pelvic floor [40].Stand with your legs apart, and check that the buttock muscles are relaxed while you squeeze the PFMs [40].

**Table 1 Tab1:** Pelvic floor muscle exercise sequences

Gestational stage	Position adopted	Type of muscular contraction	Number of contractions	Contraction sustaining time (s)	Muscle relaxation time after contraction (s)
From 20 weeks until birth	Standing	Slow	8–10	8–10	8–10
		Fast	5	1	–
	Sitting	Slow	8–10	8–10	8–10
		Fast	5	1	–
	Lying down	Slow	8–10	8–10	8–10
		Fast	5	1	–

Women will be instructed on the Knack method (Table 2). They will be taught to contract their PFMs before coughing, sneezing, lifting or bending. Women will also be asked to stop the flow of urine when they are urinating. If it is difficult to stop the initial flow, they can test themselves towards the end of urination, which is much easier. This is only a test to see whether they are using the muscles correctly. They are asked not to use urination for training, as this can interfere with the ability to empty their bladder completely [35, 39].

**Table 2 Tab2:** Knack method

Aim	3 sets of 13 pelvic floor muscle contractions lasting 8–10 s daily
Triggers (red stick-up dots)	Shower, teeth, meals, queues and so forth
The Knack	Functional bracing: grip up before cough, sneeze, lift, bend
Postnatally	As above and also incorporating good bladder habits

In order to assess the compliance rate, women in the intervention group will be provided with a diary to record their exercises daily. Women will be followed up fortnightly via text messages as reminders. Red stick-up spots will be used to remind women to do the exercises as this has been demonstrated to be effective [38].

Both study and control groups will receive routine antenatal care during pregnancy. The routine antenatal care includes verbal advice on PFME given by midwives to women at 28 weeks’ gestation. The advice is given in one antenatal visit and is known to be inconsistent and brief, as there is no structured PFME programme available. The available antenatal classes also do not cover a structured antenatal PFME training with follow up. The physiotherapy service is available to the women who are referred to a physiotherapist to receive specific physical therapy treatment.

In this study, women in the control group will not receive training on PFME from the researcher; however, they will not be discouraged from performing PFMEs. There is no dietary or lifestyle requirement or restriction as a result of participating in this study. Women in the intervention group are required to follow the PFME protocol provided by the researcher and to avoid using a different PFME protocol.

If women develop any complications related to pregnancy, they will be allowed to withdraw from the study if they are advised to do so by a doctor.

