**Fig. 3 Fig3:**
[figure not shown]
The schedual of enrollment, interventions and assessment

The secondary outcome endpoints will be examined as follows:Childbirth outcomes will include duration of the first, second and third stages of labour, fetal positions and presentation at birth; mode of birth; episiotomy and perineal trauma (1st, 2nd, 3rd and 4th degree perineal lacerations); and fetal outcomes including the APGAR score, head circumference, length and weight. Data regarding childbirth outcomes and fetal outcomes will be obtained from the hospital database after birth.Urinary incontinence symptoms and specific quality-of-life measures will be assessed using the short forms of the Urogenital Distress Inventory (UDI-6) [43] and the Incontinence Impact Questionnaire (IIQ-7) [43] at the time of booking at 20 weeks’ gestation, at 36 weeks’ gestation and also at 3 months following birth. The short forms of the UDI-6 and IIQ-7 are composed of six and seven questions, respectively. They are validated self-report questionnaires and have been shown to have a high degree of correlation with the longer forms of these questionnaires. Both questionnaires are recommended by the second international consultation on incontinence [44]. The UDI-6 is a six-item symptom inventory, specific to symptoms associated with lower urinary tract dysfunction, and combines information on stress, obstructive and discomfort symptoms. The IIQ-7 is a seven-item life-impact assessment instrument specific to UI, and covers separate domains of physical activity, travel, social/relationships and emotional health. Both measures were developed for self-administration and are intended to be used in combination. Women rate how much they experience impaired function of UI and the extent to which this UI affects their daily functioning with four response options per item (0 = “not at all”; 1 = “slightly”; 2 = “moderately”; 3 = “greatly”). For this study, we maintained the scoring procedure as described by the original developer: if more than two items are missing, a total score is not to be calculated. The mean score of items is multiplied by $$ 33\raisebox{1ex}{$1$}\!\left/ \!\raisebox{-1ex}{$3$}\right. $$ to convert to a 0–100 scale. Higher scores indicate more symptom distress (UDI-6) or more impact on daily life (IIQ-7) [45].Faecal incontinence (FI) symptoms will be assessed using a Waxner short form of faecal incontinence questionnaire [46] and has been validated in Australia [47]. The Waxner classification is a 20-point scale used to determine the severity of faecal incontinence and is widely used in Europe [46]. The Waxner questionnaire consists of five questions addressing solid, liquid, gas, changing underwear and lifestyle. Excellent or a score of 0 means continent to liquid and solid stool. Fair means incontinent to liquid and flatus. Poor or a score of 20 means total incontinence [46].

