To assess the compliance rate, women will be given a diary to record their PFME daily. These data will be collected and recorded monthly by the researcher.

All questionnaires are self-report questionnaires and will be delivered electronically through the REDCap electronic system [51] to women unless they choose to receive hardcopies. The first researcher ([name]) will collect the data. All missing data will be reported with reasons given and patterns of occurrence explored. If women withdraw from the study, no more additional information will be collected; however, the personal information already collected will be retained to ensure that the results of the research project can be measured properly and to comply with the law.

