### Sample size

The sample size of this study was calculated based on the recent research available on the impact of PFME on SF in the postpartum period. Using information from this study [52], a total FSFI score of 28.9 ± 4.54 in the intervention group after PFME and 26.6 ± 4.40 in the control group and a standard deviation of 4.54 in both groups, a sample size of minimum of 62 in each arm would be required to detect a 9% difference in FSFI scores between groups (80% power and *α* = 0.50). The treatment and control ratio is 1. Allowing for 20% attrition during pregnancy, around 160 women are needed to be recruited. However, considering the possibility of a higher rate of withdrawal at 3 months after birth and anticipating 30% attrition after birth, 200 women will be randomised.

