### Statistical analysis

Analysis of the primary and secondary outcomes will be based on an intention-to-treat basis, which will include withdrawal and losses to follow up. Descriptive statistics including numbers and proportions, and means and standard deviations will be used. Primary analysis including chi-square and Student’s *t* tests will be used to examine group differences in the primary and secondary outcomes. Repeated ANOVA will be used in order to assess within-patient correlation. Effect sizes will be reported with 95% confidence intervals, and results will be considered significant if *P* < 0.05. Data will be analysed using SPSS.

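### A pregnancy complication can take a woman out of the whole study rather than just the exercise, and obtainable outcomes are then not collected

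*Protocol article*

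**What the plan says.** Two sentences in the protocol article act together.

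- **Methods, Intervention used in this study** (last paragraph): women who develop "complications related to pregnancy, they will be allowed to withdraw from the study if they are advised to do so by a doctor". No arm is named. The sentence permits leaving and does not require it.
- **Methods, Outcome measures and data collection** (last paragraph): "If women withdraw from the study, no more additional information will be collected". Data already held are kept.

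Other statements bear on the point:

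- The FSFI is due at 20 weeks, 36 weeks and 3 months after birth, by self-report questionnaire, normally sent electronically.
- For the birth results: "Data regarding childbirth outcomes and fetal outcomes will be obtained from the hospital database after birth".
- Statistical analysis: "Analysis of the primary and secondary outcomes will be based on an intention-to-treat basis, which will include withdrawal and losses to follow up".
- On missing data: "All missing data will be reported with reasons given and patterns of occurrence explored".
- Randomisation and blinding: "The other care providers, including midwives and doctors, will be blind to the group allocations". The women themselves know their arm.
- Study design: "The trial design incorporates treatment flexibility".
- Sample size: "anticipating 30% attrition after birth, 200 women will be randomised".

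**The concern.** The clinical reason for the exit is a pregnancy complication, and the most a doctor could need to stop is the exercise. The sentence instead offers an exit from the study, and the withdrawal rule turns that exit into an end of data collection. A control woman has no study exercise to stop, so in her case leaving achieves nothing except loss of data.

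The outcomes at stake include mode of birth, length of labour, perineal trauma and postpartum sexual function. A complication plausibly relates to all of these, so women lost by this route may differ systematically from those who stay. An intention-to-treat analysis cannot include outcomes that were never collected. Reporting reasons and patterns describes the gap without filling it. Imputation, if the analysis plan provides for it, would put assumptions in place of data that could have been had.

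**Working it through.** **1. What one exit costs.** A woman who leaves between baseline and 36 weeks loses 2 of 3 FSFI measurements and, as the withdrawal rule reads, her birth record. This follows from the schedule in Table 3 and needs no assumption.

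**2. The plan's sample size.** Inputs from the Sample size section: difference 28.9 − 26.6 = 2.3 points, SD 4.54, power 80%, ratio 1:1. Alpha is printed as 0.50. I use two-sided 0.05, which matches the P < 0.05 criterion under Statistical analysis and is the value that gives the stated figure.

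n per arm = 2 × (1.96 + 0.842)² × 4.54² / 2.3² = 61.2, rounded up to 62. The plan's 62 per arm (124 in all) is reproduced.

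**3. Does the attrition allowance protect power?** 200 × 0.30 = 60 lost, leaving 140, or 70 per arm. The need is 124, so 140 − 124 = 16 more women could leave. Power of the two-sample t test:

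| Women per arm | Power |
|---|---|
| 70 | 84.5% |
| 62 | 79.9% |

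No loss of power is claimed.

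**4. Possible bias (illustration only).** The document gives no complication or exit rate. I assume 100 women per arm, a caesarean rate of 30% overall and 60% in those who leave, and an FSFI mean in those who leave that is 0.5 to 1 SD (2.27 to 4.54 points) below the full arm's mean. With m exits in an arm:

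- caesarean rate among those who stay = (30 − 0.6m) / (100 − m)
- upward shift in the FSFI mean among those who stay = m × δ / (100 − m)

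| m | Caesarean rate, those who stay | FSFI shift, δ = 2.27 | FSFI shift, δ = 4.54 |
|---|---|---|---|
| 3 | 29.07% | 0.070 | 0.140 |
| 5 | 28.42% | 0.119 | 0.239 |
| 7 | 27.74% | 0.171 | 0.342 |
| 10 | 26.67% | 0.252 | 0.504 |

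*Unequal exits, 7 v 3 (10 in all):*

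- Caesarean difference: 29.07 − 27.74 = 1.33 points. Standard error √(2 × 0.3 × 0.7 / 100) = 6.5 points.
- FSFI difference: 0.171 − 0.070 = 0.10, up to 0.342 − 0.140 = 0.20 points, which is 4.4% to 8.8% of 2.3. Standard error at 70 per arm: 4.54 × √(2/70) = 0.77.

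*Equal and alike exits, 5 v 5 or 10 v 10:* the shift in the difference is 0. Each arm's caesarean rate still reads low, by 30 − 28.42 = 1.6 or 30 − 26.67 = 3.3 points.

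**The case against.** The case for leaving the wording alone has four parts.

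*The rule is permissive and doubly conditional.* It needs a complication and a doctor's advice, and nothing says that a woman who stops exercising must leave. The stated flexibility of treatment fits with staying in. This is correct, so the loss is possible and not certain. But the only route the article states for a woman so advised is out of the study.

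*Graded withdrawal belongs in the full protocol and consent form, which are not shown.* That holds for the detail of consent options. It does not cover the two sentences that are shown, which name the study as the thing left and end all collection.

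*Exits should be few and balanced.* Entrants are low risk, pelvic floor exercise is considered safe, and doctors are blind. Much of this stands: blinding removes most of the reason to expect different advice by arm. It does not exclude a difference, since women know their arm and may tell the doctor.

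*The figures are small and assumed.* They are. Even with 7 v 3 exits, both shifts are about a quarter of a standard error or less, and with equal exits only the description of each arm suffers. This limits how serious the point is. It gives no reason to forgo data that can be obtained.

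**Conclusion.** The concern holds. The doctor-advised exit is tied to the study instead of the exercise, and the withdrawal rule then ends collection of outcomes that do not depend on exercising and that the intention-to-treat aim needs.

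The per-woman loss is certain for anyone who leaves by this route before 36 weeks. The number of such women is unknown and probably small. Power is not threatened on the plan's own attrition figures. Expected bias in the group comparison is about zero if exits are equal and alike, and modest under the imbalance illustrated, which rests wholly on assumed rates. Whatever the balance, both arms' follow-up and birth results would describe women selected towards uncomplicated pregnancies. The change should be made because the loss is avoidable and potentially informative. The trial can run without it. Confidence is medium, because the exit rate cannot be determined.

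**What to change.** Reword the sentence under Intervention used in this study: on a doctor's advice a woman may stop or pause the exercise, and she stays in follow-up. She is still sent the 36-week and 3-month questionnaires, and her birth data are still taken from the hospital database.

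Under Outcome measures and data collection, limit the end of collection to women who withdraw consent to data collection, asking separately about questionnaires and hospital records. Record stopping the exercise and leaving follow-up as separate events.

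The cost is two sentences of protocol and consent wording and a short ethics amendment. Recruitment began in February 2018, so women already enrolled may need to be asked for consent again. Some women would be contacted at a difficult time and may decline. Sample size, instruments and schedule do not change.
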